## Oversight and monitoring

### Composition of the coordinating center and trial steering committee [5d]

The study team (consisting of three sport scientists, a research manager, and a physician) is responsible for the day-to-day conduct of the trial and will meet regularly at least quarterly, across the course of the trial, making all relevant decisions regarding the study. The sport scientists specifically are in charge of patient enrolment and conduction of the 6-week SMART-intervention as well as the diagnostics. The physician is responsible for the clinical assessment of the patients during patient enrolment. The study team itself is in charge of the project administration.

### Composition of the data monitoring committee, its role and reporting structure [21a]

The trial will be monitored by the study investigators. There will be regular check-ups with the participants during the intervention to eventually adapt the training protocol.

A formal data monitoring committee is not needed for the current trial. This is because the participants are not exposed to significant harms and because of its short duration (6 weeks).

### Adverse event reporting and harms [22]

The investigators stay in regular contact with the participants. Adverse events, like recurrent ankle sprains, will be documented at each follow-up visit. Recurrent ankle sprains have an influence on the chronic instability of the ankle and will therefore be reported in future publications. Participants are asked to report significant worsening of their ankle by contacting the study team immediately, so that physical examinations can be guaranteed.

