### Intervention description [11a]

The SMART intervention was developed to provide a systematic rehabilitation concept for acute LAS. It is a sensorimotor training program which addresses various functional training domains to regain ankle joint function and stability [5, 11]. SMART is an acronym and consists of the following domains: S = Sensory Stimulation, M = Mobilization, A = Activation and Balance, R = Resistance and Re-Integration, T = Transfer to Function and Performance. A typical rehabilitation process runs through different phases with different goals. Therefore, there is a progress in focus between the five domains over the 6 weeks, as described below: The domains S and M are present across the whole intervention. In week 1 and 2, the main focus is on the A domain, in weeks 3 and 4 on the R domain, and in weeks 5 and 6 on the T domain.

During the 6-week intervention period, five training sessions are held per week each lasting approximately 30–45 min. The detailed training plan of the SMART intervention can be found in the supplemental material. In the beginning, the training sessions will be center-based, to ensure individual feedback and to give participants the possibility to familiarize with the training concept. Across the 6 weeks, the training is shifting towards more home-based sessions, since the participants do not need the close supervision anymore (weeks 1–2: 6 × center-based and 4 × home-based; weeks 3–4: 4 × center-based and 6 × home-based; weeks 5–6: 2 × center-based and 8 × home-based). There are regularly video calls with the sport scientist to meet up with the participants and provide feedback.

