### Participant timeline [13]

The process of enrolment (eligibility screen, informed consent, basic sociodemographic data) will take place in the first 2 weeks after initial injury. At t1, before the 6-week intervention, participants will be allocated and there will be psychometric questionnaires as well as all strength, postural control, gait/run, and jump testing. The same will be done at t2 after the intervention. While t3 is just a follow-up done by email, t4 includes the full diagnostic standard as in t1 and t2 (Fig. 1).

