### Plans to promote participant retention and complete follow-up [18b]

As already mentioned in 11b, there are multiple strategies to promote the participant’s adherence to the intervention. There will also be check-ups during the 6-week-intervention. These are video calls which are attractive to the participant since they provide a low-threshold access to the intervention. These check-ups help to guide the intervention and eventually adapt it. The 6-month follow-up will be done via email with Heartbeat (service to collect questionnaires). By this, the participants can answer the questionnaires from home. Heartbeat will send reminders to the participant in case of not answering the questionnaire. There will be a list of all expected outcomes for the patients. The participants will get an expense allowance after 6 weeks and 12 months. By dividing disbursement of the expense allowance to the 6-week and 12-month time points, patients are further encouraged to complete their follow-up. In case a participant does not want to complete the follow-up, especially the diagnostic, we give the option to just complete the questionnaires via Heartbeat.

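### Recurrent sprains are to be recorded at follow-up visits, but the 6-month follow-up has no visit and the 12-month visit can be replaced by questionnaires, so re-sprains are likely to be under-recorded in both arms

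*Protocol article*

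**What the plan says.** Section [22] sets the recording rule: "Adverse events, like recurrent ankle sprains, will be documented at each follow-up visit". It also commits to publication: "Recurrent ankle sprains have an influence on the chronic instability of the ankle and will therefore be reported in future publications".

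The same section gives two further routes, neither limited to one arm. One is general: "The investigators stay in regular contact with the participants". The other relies on the patient: "Participants are asked to report significant worsening of their ankle by contacting the study team immediately, so that physical examinations can be guaranteed".

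The schedule is in Participant timeline [13]: "While t3 is just a follow-up done by email, t4 includes the full diagnostic standard as in t1 and t2". The retention section [18b] adds that, for participants who do not want the 12-month diagnostics, "we give the option to just complete the questionnaires via Heartbeat". The sections on secondary outcome assessment [18a] and Data management [19] name CAIT and FAAM as the instruments collected through Heartbeat. No re-injury item is mentioned.

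On contact during the six weeks, Intervention description [11a] gives SMART a schedule of centre-based sessions and adds: "There are regularly video calls with the sport scientist to meet up with the participants and provide feedback". The comparator section [6b] describes physiotherapy as needed for NORMT and no scheduled contact with the study team between t1 and t2. Section [11c] pays SMART participants 50 € at 6 weeks and 50 € at 12 months, and NORMT participants 25 € at each.

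**The concern.** A rule that records events at visits works only where there are visits. After t2 the plan has one scheduled visit, at t4, and that visit may be waived. A sprain in between is captured on schedule only if the patient attends t4 and remembers it. CAIT and FAAM are described as measures of perceived function and impairment. A low score may reflect a new sprain, but it does not record one.

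Recurrent sprain is the only adverse event the plan names. It is also one of the features by which the introduction characterises chronic ankle instability, the condition that motivates the trial. Counts will be published from an open-label two-arm trial, and readers will set them side by side even though no test is planned. Incomplete counts weaken the safety information. If completeness also differs by arm, they could mislead about direction.

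Data collection cannot be repaired at the analysis stage, so the point belongs with the protocol.

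**Working it through.** The plan gives no re-sprain rate, event count or power for this event, so there is no stated figure to reproduce. The check sets the recording rule against the schedule, and then bounds the between-arm risk under labelled assumptions.

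**1. Rule against schedule**

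| Time point | Visit? | Scheduled route for a sprain record |
|---|---|---|
| t2 (after 6 weeks) | Yes, both arms | Visit |
| t3 (6 months) | No, e-mail | None named |
| t4 (12 months), full | Yes, both arms | Visit, by recall since t2 |
| t4, questionnaire only | No | None named |

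**2. Length of the gap.** The visible text does not say from when the 12 months are counted.
- From t1: 52 − 6 = 46 weeks, or 46/52 × 12 = 10.6 months from t2 to t4.
- From injury, with t1 two weeks later (Objectives [7]): 52 − 2 − 6 = 44 weeks, or 10.2 months.

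Either way the gap is somewhat over 10 months.

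**3. Under-recording, both arms (illustration).** Assume sprains are spread evenly over 52 weeks from t1. Then 46/52 = 88% of them fall after t2. The share of questionnaire-only completers is not given. Borrowing the plan's 20% loss-to-follow-up allowance purely as an example, 0.20 × 0.88 = 18% of all sprains would have no scheduled record, before any recall loss. At an assumed true risk of 10% and 41 patients per arm (4.1 sprains), that is about 0.7 sprains per arm.

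**4. Contact difference between arms.** SMART has 6 + 4 + 2 = 12 centre-based sessions plus an unstated number of video calls. None are described for NORMT. Sections [18b] and [21a] mention check-ups without naming an arm, but give their purpose as guiding and adapting the training. After t2 the planned schedule is the same in both arms.

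**5. Size of the contact effect (assumptions).** Suppose true risk is equal, every sprain heard at a SMART contact is recorded, 95% of sprains are captured in SMART during the six weeks, and a fraction *s* is captured in NORMT then and in both arms afterwards. With events spread evenly, the six-week share is 6/52 = 0.115, and

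apparent ratio (SMART/NORMT) = 1 + 0.115 × (0.95/*s* − 1).

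- *s* = 0.80: 1 + 0.115 × 0.188 = 1.02
- *s* = 0.70: 1 + 0.115 × 0.357 = 1.04
- *s* = 0.60: 1 + 0.115 × 0.583 = 1.07

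At 10% true risk and 41 per arm the excess recorded in SMART is 4.1 × 0.115 × (0.95 − *s*), which is 0.07 to 0.17 events.

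If the capture difference were applied to the whole year, the ratio would be 0.95/*s* = 1.19 (*s* = 0.80) to 1.58 (*s* = 0.60), or 3.9 recorded events against 3.3 to 2.5. The schedule does not support that extension, because the contact difference ends at t2.

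**6. Payments.** The totals are 50 + 50 = 100 € for SMART and 25 + 25 = 50 € for NORMT. If payment affects attendance at the full t4 visit, NORMT would have more questionnaire-only completers and fewer scheduled sprain records. Nothing in the document allows this to be sized.

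**The case against.** The strongest defence has four parts.

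- **Condensed article.** Adverse-event forms and item lists are usually in the full protocol, and the phrase about follow-up visits may be loose wording that includes the e-mail follow-up. This is fair, and it is one reason for low severity. The point does not rest on silence alone, however. The article states a positive rule and a schedule, and the two do not fit. If a re-injury form already exists at t3 and for questionnaire-only completers, one sentence resolves it.
- **Other capture routes.** Section [22] also provides for regular contact and immediate self-report in both arms, so it would be wrong to say that sprains are recorded only at visits. This stands. But the frequency and content of the contact are not given, and self-report is tied to significant worsening, a threshold that milder re-sprains may not reach.
- **Same gaps in both arms.** The t3 and t4 arrangements are the same by design. They cause under-recording and recall loss, and do not by themselves create a difference between arms. This stands.
- **No comparison planned.** Recurrent sprain is not in Table 1 of Outcomes [12], and no test of it is specified. The plan promises reporting. This stands too, although published counts by arm will still be compared informally.

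A reader might infer more: that SMART's extra contacts make the re-sprain comparison unequally ascertained, with a ratio of 1.19 to 1.58 against SMART. The document does not support this. It nowhere says that sprains mentioned at training contacts enter the adverse-event record. If recording happens at visits, both arms have the same planned recording points. A sprain in the six weeks can still be recorded at t2 in either arm. The ratios also require a six-week contact difference to act over a full year.

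**Conclusion.** The recording rule for recurrent sprains does not match the follow-up schedule. As written, the roughly 10 months between t2 and t4 depend on recall at one visit, and questionnaire-only completers have no scheduled sprain record after t2. The likely result is under-recording in both arms. Its extent depends on recall and on the number of questionnaire-only completers, neither of which the document gives.

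Unequal ascertainment is a secondary risk and not an established fact. Its size cannot be determined from the document. For the contact difference it is probably small: about 1.02 to 1.07 as an apparent ratio, assuming equal true risk, even event timing, 95% capture in SMART during the six weeks and 60% to 80% otherwise. Any effect of unequal payments on t4 attendance would act in the same direction, towards more recorded events in SMART, and cannot be sized.

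Severity is low. The primary CAIT analysis is unaffected, and re-sprain is not a listed outcome. The change is still worthwhile, because the plan commits to publishing this event and the remedy is cheap.

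**What to change.** - Add the same structured re-injury items to the Heartbeat questionnaire at t2, t3 and t4 in both arms: new sprain since the last assessment (yes/no), side, date, and care sought. Include participants who complete t4 by questionnaire only.
- Reword section [22] so that recording is tied to each assessment, whatever its mode.
- Base reported re-sprain counts by arm on these items, and state how many participants answered them at each time point.
- List events learned from training sessions or video calls separately, so that they do not enter the counts by arm.

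The cost is a few extra items in a platform that already sends reminders, a short amendment notified to the ethics committee and registry, and slightly more burden for patients. For participants already past t3 when the amendment takes effect, the t4 items would have to cover the whole interval since t2, and the report should say so.

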### Frequency and plans for auditing trial conduct [23]

There are no plans for independent auditing of trial conduct.

### Plans for communicating important protocol amendments to relevant parties (e.g., trial participants, ethical committees) [25]

Any change to the trial protocol will be communicated with the ethical committees and trial registry.

### Dissemination plans [31a]

We will disseminate our research with academic and professional audiences via presentations at conferences and publication of findings in high-impact journals.

## Discussion

The study has two main aims which are going to address: The primary aims are to investigate the effectiveness of a sensorimotor training intervention in contrast to standard therapy after an acute LAS on perceived ankle joint function. We hypothesize that patients treated with SMART show a better subjective outcome in perceived ankle joint function than patients treated with NORMT. Since currently, there is a high rate of acute LAS developing a CAI, this study has the potential to improve the healthcare for LAS patients in the long term. The data of this study might therefore be used for a future standardized evidence-based rehabilitation-concept being able to reduce the long-term CAI rate.

The secondary aim is to determine an effective test battery for the valid measurement of a functional ankle instability. This will be achieved by comparing the injured patients with an uninjured control group. Therefore, it might be necessary to not only compare the acute state (t1) with the uninjured control group but also the time point after the intervention (t2). The goal is to identify specific tests which are able to display an abnormal trend of the ankle function. These would then further allow to navigate through LAS rehabilitation of future patients.

Additionally, it might be possible to identify risk factors in the test battery predicting a CAI. Eventually, some patients have a higher probability to develop a CAI. These identified risk factors could then be used to screen patients after the injury and monitor them more closely.

## Trial status

The recruitment started on 3 January 2022, and the trial protocol is still used in its original version. The recruitment phase is estimated to be completed in January 2024.

## Data Availability

The data is maintained on a hospital server that only the investigators will have access to.

## Abbreviations

CAIT: Cumberland Ankle Instability Tool
COP: Center of pressure
FAAM: Foot and Ankle Ability Measure
LAS: Lateral ankle sprain
MVC: Maximal voluntary contraction
ROM: Range of motion
SEBT: Star Excursion Balance Test
SPM: Statistical parametric mapping
TTB: Time-to-boundary
